### Health Insurance Claims Data

Annually, the UA Study Coordinator will create a coded, numeric list of study participants, who are employees or adult dependents of participating employer groups, to send to their health plan. This list will enable the health plan to generate and return a file of otherwise de-identified health claims data. Study participants will be identifiable (a partial waiver of protected health information data was granted by the UA Institutional Review Board) so that healthcare utilization data can be matched to their other study data, and the remainder of the file will be used to generate the matched control groups. The initial data request will cover one year prior and one year after clinic enrollment for study participants, and a comparable 2-year period for non-participants.

### Fidelity monitoring measures

#### Patient feedback questionnaire

Patient experiences of the various dimensions of integrative medical care will be assessed for their same-day care by a 51-item “How is UAIHC doing?” Patient Version questionnaire developed for the fidelity study. Dimensions of the questionnaire include access to care, whole person care, promotion of self-care and wellness, practitioner communication style, shared decision-making, trust in the practitioner, perceived practitioner empathy, perceived health partnership, and socio-demographic information. Items were derived from established measures of primary care quality: the Consumer Assessment of Healthcare Providers and Systems (CAHPS) Surveys 2.0 Adult visit and Patient-Centered Medical Home versions [50,57], the Ambulatory Care Experiences Survey (ACES) [73], and the Consultation and Relational Empathy measure (CARE) [74]. Several items were developed for the study to tap patient experiences of IM care not assessed in existing instruments. It is estimated that it will take 10–15 minutes for patients to complete this questionnaire.

### Patient chart extraction

A number of items will be extracted from a random sample of 10 de-identified patient charts at the end of each fidelity measurement month for patients seen during that month. The clinic staff will generate a list of the medical record numbers of all enrolled patients seen during the last month and report the total number (N) to the research team. The research team will use a simple computer-based randomization scheme to create an equal length list consisting of “select” and “don’t select” statements. Clinic staff will then match these lists and pull and de-identify those charts whose medical record numbers match up with the “select” statements. The data to be extracted by the research team are intended to assess IM whole person care (e.g., a review of systems beyond those typically assessed in conventional care including domains such as spirituality, social support, family and work stressors, etc.), the patient-practitioner partnership agreement, the mix of conventional and CM therapies used, and lifestyle recommendations over the past month. Visit lengths are also recorded.

### Practitioner experiences survey

Practitioner experiences working in the UAIHC will be assessed using the 27-item “How is UAIHC doing?” Practitioner Version questionnaire developed for the fidelity study. Dimensions of the questionnaire assess the team care climate of the clinic, practitioners’ stress and self-care practices, and practitioners’ feedback on how practicing in the UAIHC model may affect their clinical care. The Team Climate Inventory (TCI) [75], a single-item on practitioner burnout [76], as well as additional individual items to account for IM principles will be administered. It is estimated that it will take 10–15 minutes for staff to complete this questionnaire.

### Qualitative/case study data

The patients who have been selected for and agreed to case study interviews will participate in a 20–30 minute semi-structured interview immediately after each of the outcomes data collection points. The patient’s outcome results over time will be available to the interviewer, and the interview will focus on the patient’s experience of care at UAIHC and what the patient believes has contributed to any health changes seen in the course of treatment. These interviews will be either done by phone or in person, and will be audiotaped and transcribed.

### Analysis

Five sets of inter-related analyses are planned for these data. The first will be a descriptive study based on the demographics and baseline values of the first patients (e.g., first 200) who join the study. The purpose of this study and report is to document the characteristics, diagnoses, symptoms and expectations of those patients who choose to enroll in this integrative primary care clinic. Where possible, patient characteristics, diagnoses and symptoms will be compared to those seen nationally and statewide in primary care using data from the National Ambulatory Medical Care Survey (NAMCS) [77]. Basic descriptive statistics will be used. When comparisons are possible, will utilize *t* tests for independent samples for continuous data, and χ^2^ tests for frequencies.

The second analysis will use the fidelity monitoring data to describe clinic operations and to describe how this IM primary care clinic developed over time. Since these are measures of the intervention itself (the clinic), by design the patient fidelity sample measurements over time will not be taken on the same individuals. Therefore, data will be analyzed using simple descriptive statistics. The results will also be examined for trends using regression analysis with time (either continuous or as a set of dummy variables) as the main explanatory variable, and significant *t* tests for the time coefficient(s) as an indication of significant change over time in clinic operations. Components of the clinic model that change significantly over time and/or that contribute to the outcomes will be considered as covariates in the two outcomes studies described below [24].

The third analysis will involve data from the case study participants. The narrative data from the transcribed, audiotaped semi-structured interviews will be content analyzed using dedicated qualitative data analysis/text management software (*Atlas-ti*), and key concepts will be categorized into salient themes and patterns. Those results will be related to each participant’s reported and recorded outcomes to look for insights into clinic impacts and operations.

The fourth and fifth analyses will be the main outcome studies. The fourth study will be a prospective cohort study of the changes in outcomes from baseline to one year for all patients in the outcomes sample. The primary outcome for this analysis will be health-related quality of life measured in three ways (SF-6D [78], and the physical and mental component summary scores, all derived from the SF-12), with the other outcomes as secondary measures. The main comparison will be baseline to 12-month outcomes and the univariate analyses will use paired *t* tests for continuous data, and use the McNemar test for frequencies [79]. The data will also be examined for patterns of change over time in key outcomes, and the determinants of those patterns, using hierarchical linear modeling (HLM) techniques [80-82]. Fidelity measures with significant changes over time will be used as covariates [24] in these models, as well as other explanatory variables such as demographics, participants’ membership level and baseline diagnoses. If participant numbers for each of the five targeted condition allow, condition-specific outcomes will be examined for each. These same analyses will be applied to other secondary outcomes such as CVD event [70] and mortality [71] risk.

The fifth analysis will focus on the subset of patients for which health insurance claims data are available and will utilize a matched comparison design. Prior to analysis all claims data for each individual (treatment and comparison groups) will be aggregated (by summation) into per health plan member per month (PMPM) totals of paid amounts (the amount paid by the health plan to the practitioner) for each of the following cost categories: total, inpatient, outpatient, emergency room, physician, and pharmaceutical claims. Similarly, the numbers of outpatient visits, hospital stays and emergency department visits will also be aggregated for each individual. The primary outcome will be total cost. Two comparison groups from de-identified claims data will be created—one using simple matching (e.g., by age and gender) and one using propensity scores [49]. After the comparison groups have been selected, simple descriptive analyses will show average PMPM costs and healthcare utilization (including standard deviations and other measures of dispersion) pre- and post- enrollment (or an equivalent date for the comparison groups) by gender, age, baseline diagnosis and by treatment and comparison group. Because cost data tends to be highly skewed, average PMPM costs and healthcare utilization pre/post enrollment, and the change in costs and utilization pre/post between the treatment and each of the comparison groups will be reported as mean differences with confidence intervals calculated using bootstrap methods [83,84]. Because of the number of data points for each patient (e.g., up to 12 PMPM values pre-enrollment and 12 post-enrollment), HLM [80-82] will be used to estimate the pattern of change in healthcare utilization and costs over time, and to explore the determinants of those patterns. Fidelity measures with significant changes over time [24], demographics, participants’ membership level and baseline diagnoses will be included as covariates in these models. Finally, changes in costs between groups will be compared to changes in patients’ CVD risk.

Results for the last two analyses will be reported following the Strengthening the Reporting of Observational Studies in Epidemiology (STROBE) guidelines [85]. For all outcomes, the estimated treatment effects will be reported using their original outcome scale and including confidence intervals.

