### Outcomes sample

Only patients who are members at UAIHC and who meet the inclusion/exclusion criteria are eligible to enroll in this study. Participation in the study will continue for at least one year after enrollment. It is anticipated that at least 500 patients will consent to participation during the first nine months of the study. Our primary outcome for our main analysis is change in total costs (see the Analysis section below). Using the standard deviation seen in a set of healthcare utilization data from a related group, a sample size of 200 patients should be sufficient to detect a small effect size (Cohen’s d = .20) difference in total costs at a .80 power using an alpha of .05. Therefore, our expected sample size of 500 may also allow for some subgroup analysis. Inclusion criteria: 1) Enrollment in primary care (members) at UAIHC; and, 2) adults ages 18 or older. Exclusion criteria: 1) currently pregnant at time of recruitment; 2) patients who attend the UAIHC clinic as “consultation-only” patients; and, 3) significant cognitive impairment to the extent that the individual is unable to understand the consent and respond to questionnaires.

All new patients will be advised by their primary care physician that they may be eligible to participate in a study to evaluate the effectiveness of the UAHIC. Prior to checkout, patients have an exit session with the University of Arizona (UA) Study Coordinator. During this session (or if necessary, through a follow-up phone call), the Study Coordinator will explain the nature of the study and make a determination of study eligibility, and if appropriate, consent the patient. Patients who joined the UAIHC before study start (July 2013) will also have the opportunity to participate. The study will be explained at their first UAIHC visit after study start.

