### Self-report instruments – all patients

In addition to general socio-demographic data and an item on patients’ expectations of the clinic (both asked only at baseline), several factors are captured that could be seen as overall determinants of health and/or intermediate outcomes: diet, exercise, self-efficacy, stress, sleep and patient satisfaction. In addition, a number of specific (pain, fatigue, depression and anxiety) and global (quality of life, well-being, and work productivity) outcomes are captured. Each is described briefly below. It is estimated that it will take patients 15–20 minutes to complete these instruments.

• Diet quality. Diet quality is assessed by the Fruits and Vegetables module of the Behavioral Risk Factor Surveillance System [51]. Six items assess the type of fruits, vegetables, and legumes eaten in the past month and their frequency.

• Exercise & Physical Activity. Physical activity is assessed by the Exercise/Physical Activity module of the Behavioral Risk Factor Surveillance System [51]. Eight items assess the type, frequency, and duration of exercise/physical activity in the past month.

• Health self-efficacy. The Patient Activation Measure (PAM) is a 13-item self-assessment of an individual’s knowledge, skill, willingness, and confidence in managing their health and health care (activation) [52,53]. Scores stratify patients into four levels of health care activation.

• Stress. Several aspects of stress are captured. The Perceived Stress Scale (PSS) [54] is a brief measure that assesses the degree to which situations in one’s life are appraised as stressful in a global manner. Items tap how unpredictable, uncontrollable, and overloaded respondents find the stress in their lives to be. Two single items, found to strongly correlate with established multi-item measures, are used to tap the psychological response to stress and the amount of stress experienced in the past year [55].

• Sleep quality. Sleep quality is assessed by the 9-item Pittsburgh Sleep Quality Index (PSQI) [56]. The PSQI measures the quality and patterns of sleep over the past 1 month. It differentiates “poor” from “good” sleep by inquiring about seven areas: 1) subjective sleep quality, 2) sleep latency, 3) sleep duration, 4) habitual sleep efficiency, 5) sleep disturbances, 6) use of sleeping medication, and 7) daytime dysfunction.

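### The descriptive report on who enrolls in the clinic uses the first study joiners, so among pre-July 2013 members an early cut favors frequent attenders, by an amount the protocol does not let one compute

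*Protocol article*

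**What the plan says.** The Analysis section of the protocol article plans a first, descriptive report on "the first patients (e.g., first 200) who join the study". Its stated purpose is a profile (background, illnesses, complaints and what they hope for) covering "those patients who choose to enroll in this integrative primary care clinic". When suitable outside data exist, the report also has a benchmark: "patient characteristics, diagnoses and symptoms will be compared to those seen nationally and statewide in primary care", by t tests and chi-square tests against national ambulatory care survey figures.

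Outcomes sample sets out two ways into the study. New patients are told of it by their physician, and "Prior to checkout, patients have an exit session with the University of Arizona (UA) Study Coordinator", who explains the study and takes consent (by a later phone call if needed). The second way is for existing members: "Patients who joined the UAIHC before study start (July 2013) will also have the opportunity to participate". For them, "The study will be explained at their first UAIHC visit after study start".

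The section on self-report instruments for all patients includes an item on patients' "expectations of the clinic (both asked only at baseline". Data Collection defines baseline as the initial clinic visit. Outcome measures says that some baseline items come from the clinic's intake form, without saying which.

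**The concern.** The report is about people who enroll in the clinic; its sample is the earliest people to enroll in the study. For new members the two nearly coincide, and entry does not depend on how often they later come back. For earlier members, the time of study entry is the waiting time from July 2013 to their next visit. A member who attends every few weeks is reached almost at once. One who attends once a year is likely to be missed by an early cut, and one who has stopped coming is never reached.

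Two uses of the report are exposed. The comparisons with national and state primary care would treat a sample partly selected on visit frequency as a sample of enrollees. And if earlier members answer the expectations item when they join the study, they answer it after using the clinic, so it would not record what they expected when they chose to join.

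**Working it through.** **No figure in the plan to reproduce.** The 200 in the Analysis section is an example cut with no derivation. The 200 in the sample size statement is a separate calculation (d = 0.20, power 0.80, alpha 0.05): (1.96 + 0.84)² / 0.20² ≈ 196.2, so 197 on a one-sample or paired basis. It is not an input here.

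**Inputs from the protocol.** The sample is the first joiners, for example 200. Earlier members enter at their first visit after July 2013; new patients are approached at the exit session. On volume: "It is anticipated that at least 500 patients will consent to participation during the first nine months of the study".

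**Assumed inputs (not in the protocol).** M = 100 or 300 earlier members; a = 30 or 60 new members a month; mean visit rate 0.5 a month, gamma-distributed between members with shape k = 1 (CV 1.0) or k = 0.5 (CV 1.4), the same for new and earlier members; consent 70%.

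**Formulas.** An earlier member with visit rate λ has been seen by month t with probability 1 − exp(−λt). Averaging over the gamma distribution:

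- proportion of earlier members seen by t: P(t) = 1 − (1 + 0.5t/k)^(−k)
- their mean visit rate relative to all members: R(t) = [1 − (1 + 0.5t/k)^(−k−1)] / P(t)

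For k = 1 this reduces to R(t) = 1 + 1/(1 + 0.5t), which is 1.67 at 1 month, 1.50 at 2, 1.40 at 3 and 1.18 at 9. The excess fades with time, so the earlier the cut, the stronger the selection.

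The cut falls at the t that solves 0.7 × [M·P(t) + a·t] = 200. With s = M·P(t) / [M·P(t) + a·t] as the earlier members' share, the whole-sample ratio is 1 + s·(R − 1).

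**One case in full** (M = 300, a = 60, k = 1). At t = 2.16: P = 1 − 1/2.08 = 0.52, so 155.9 earlier and 129.8 new members have been approached, and 0.7 × 285.7 = 200. Then s = 155.9/285.7 = 0.55, R = 1 + 1/2.08 = 1.48, and the whole-sample ratio is 1 + 0.55 × 0.48 = 1.26.

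**Results** (first value CV 1.0, second CV 1.4; the last column assumes every earlier member returns within nine months)

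| Earlier / new per month | Months to 200 | Earlier share | Ratio, earlier members | Ratio, whole sample | Most consents by month 9 |
|---|---|---|---|---|---|
| 100 / 30 | 6.9, 7.3 | 27%, 23% | 1.22, 1.47 | 1.06, 1.11 | 0.7 × 370 = 259 |
| 100 / 60 | 3.7, 3.9 | 23%, 19% | 1.35, 1.66 | 1.08, 1.13 | 0.7 × 640 = 448 |
| 300 / 30 | 3.3, 4.0 | 65%, 58% | 1.38, 1.65 | 1.25, 1.38 | 0.7 × 570 = 399 |
| 300 / 60 | 2.2, 2.4 | 55%, 48% | 1.48, 1.83 | 1.26, 1.40 | 0.7 × 840 = 588 |

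Simulation of the same settings gives the same ranges.

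**Check against the protocol's own volume.** Only the last row can reach 500 consents in nine months (550 or 522 once non-returners are allowed for). But 80 new members a month with few earlier members reaches it too: 0.7 × 720 = 504 with none, 0.7 × 770 = 539 with 50. The whole-sample ratio is then 1.00 with none and 1.04 to 1.07 with 50. So the protocol's expected volume fits both a negligible and a material selection.

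**Different assumptions.** A second simulation used 6 visits a year, CV 0.5 to 1.0, 40 new members a month and 60% or 100% consent. It gave a mean in the first 200 of 6.0 with no earlier members, 6.0 to 6.3 with 50, 6.2 to 7.5 with 200, and 6.6 to 8.9 with 400. The last is 8.9/6.0 ≈ 1.5, so 1.4 is not a ceiling. With earlier members present and visit rates varying, the direction was always the same.

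**The case against.** The strongest reply is that the size is unknown and may be trivial. The protocol calls the clinic new and says member enrollment is unknown; with few earlier members nothing of note happens. That stands, and it is why no single figure can be given.

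Second, visit frequency is not what the report describes. A reader might infer that the report will overstate diagnoses and symptoms. The protocol does not support that: it gives no relation between attendance and illness. The membership tiers bundle between 5 and 20 complementary-medicine visits, plus coaching and classes, so frequency may partly reflect the tier bought. This also stands.

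Third, a reader might infer that earlier members' expectations are necessarily colored by experience of the clinic. The protocol leaves this open. Baseline is defined as the initial clinic visit and some baseline items come from the intake form, so the item may have been answered before any care. What stands is that the article does not say which.

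Fourth, the 200 is only an example, and table layout belongs in an analysis plan. That is fair for layout. But sampling by order of joining the study is stated in the article, and any early cut made that way has the same property.

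Finally, earlier members also chose to enroll, so dropping them would lose part of the stated target population. That stands and shapes the fix.

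**Conclusion.** The point holds as a mechanism with a known direction and an unknown size. Read together, Outcomes sample and Analysis imply that an early cut by study entry over-represents frequent attenders among members from before July 2013. This needs only that such members exist and that visit rates vary. The whole-sample ratio of visit frequency is about 1.0 if earlier members are few and up to about 1.4 under the main assumptions; the number of earlier members, visit rates, consent and inflow are all assumed.

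Any distortion of diagnoses or symptoms, or of the expectations item, is possible but not established. It would also be wrong to carry the point over to the quality-of-life or cost analyses: those do not use the first-joiners cut. This is a minor point about one descriptive report and its external comparisons, worth settling because the remedy is simple.

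**What to change.** In the Analysis section, define the descriptive report by joining date:

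- Show consecutive new members (consented at or after their first visit) and earlier members in separate columns.
- Run the national and state comparisons on the new members, with the pooled sample as a sensitivity analysis.
- Do not pool the expectations item unless earlier members' answers were recorded at their initial clinic visit.

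Earlier members stay in the report, so no part of the target population disappears from it.

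The change is one of wording, but it has a price. At a given date there are fewer new members than joiners overall. If 200 new members are wanted, the report comes later: under the same assumptions, 200/(0.7 × 60) = 200/42 ≈ 4.8 months to 200/(0.7 × 30) = 200/21 ≈ 9.5 months, against about 2.2 to 7.3 months for the pooled sample. The slow end is slightly past the nine-month recruitment window. Since 200 is only an example, a smaller number of new members would also do. The external tests would then speak for new enrollees only, and the report should say so.

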### Fidelity clinic personnel sample

The UA Study Coordinator will enroll UAIHC personnel at study start by sending an e-mail with a link to the secure URL address and password information for the informed consent form. Assessments will be on the same schedule as for patient fidelity (see Data collection below). A total of 15–20 clinic personnel (the entire UAIHC staff) will be enrolled in the fidelity study. The same consent process and incentive will be used as for the fidelity patient sample.

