### Data Collection

For the outcomes evaluation, data will be collected from patient charts and self-reports at four intervals—baseline (initial clinic visit), and at 3-, 6-, and 12-month follow up periods. Participants will receive a reminder email one week before each data collection due date. Baseline data will be due within one week of enrollment. In the email they will be directed to a secure website where they can access and complete the outcomes data collection instrument. If participants have not entered their data within 3 days of their due date, they will receive another reminder email, and those who have not entered their data within another 3 days of their due date will receive a call from the UA Study Coordinator. Healthcare utilization and cost data from healthcare claims will be obtained from their employer with study participant consent. These data will be collected for one year before and one year after clinic enrollment approximately 3 months after the 12-month follow up period to allow time for all incurred claims to be recorded. De-identified claims data for the comparison groups will be collected for the same period of time with “baseline” being defined by the average start date of study participants.

Because the intervention may change over time as clinic operations start up and mature [21], fidelity monitoring data will be collected monthly from study start for 6 months, then quarterly for 6 months, and then semi-annually. Patient-reported fidelity data will be gathered on a single randomly chosen day of the last week of the data collection month from all patients seen at the UAIHC clinic that day. This day will be selected by the UA research team using a simple computer generated randomization scheme and delivered to the UA Study Coordinator the week before the data collection week. A self-administered patient version of the “How is UAIHC doing?” questionnaire will be used for patients. For clinic personnel, fidelity data will be collected during the last week of each fidelity data collection month using an online self-administered practitioner and staff version of the “How is UAIHC doing?” questionnaire. Data from audits of randomly selected, de-identified patient charts and of administrative records will also be used to assess indicators of model implementation.

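### The reason given for the fidelity trend test covers patients only; the same 15–20 staff are surveyed at about 10 waves, so their trend needs a repeated-measures model

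*Protocol article*

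**What the plan says.** In the protocol article's Analysis section, the fidelity plan opens with its scope: "The second analysis will use the fidelity monitoring data to describe clinic operations". It then gives its reason for a simple approach: "by design the patient fidelity sample measurements over time will not be taken on the same individuals". From this follow descriptive statistics and then "regression analysis with time (either continuous or as a set of dummy variables) as the main explanatory variable", with "significant *t* tests for the time coefficient(s) as an indication of significant change over time in clinic operations".

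Fidelity data also come from staff. Under Fidelity clinic personnel sample, "A total of 15–20 clinic personnel (the entire UAIHC staff) will be enrolled in the fidelity study"; enrolment takes place at study start and the assessment schedule is the patients' schedule. Data Collection confirms this: "For clinic personnel, fidelity data will be collected during the last week of each fidelity data collection month". The schedule is monthly for six months, quarterly for six, then semi-annual, in a two-year study. On the content of the staff survey, Practitioner experiences survey says: "Dimensions of the questionnaire assess the team care climate of the clinic". It also covers stress, self-care and burnout.

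The Analysis section names no separate method for the staff survey. It names hierarchical linear modelling (HLM) for the repeated patient outcomes and the monthly costs, but not here.

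**The concern.** The reason offered for the method is true of one data source and untrue of another that the same analysis covers. The patient questionnaire is a series of cross-sections. The staff questionnaire is a panel of the same people. A regression on time that treats 150 to 200 staff responses as coming from different people uses the wrong reference variance for the slope.

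The test has a use beyond description. The second analysis takes a significant time coefficient as the sign that clinic operations changed. The fourth and fifth analyses then use fidelity measures with significant change as covariates in the quality-of-life and cost models. A miscalibrated p value can therefore affect both how the clinic's development is described and which staff measures enter those models.

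**Working it through.** **Inputs.** From the article: m = 15–20 staff, and 6 + 2 + 2 = 10 waves in two years, so 15 × 10 = 150 to 20 × 10 = 200 responses. Assumed: waves at months 1–6, 9, 12, 18 and 24, full response, no turnover, and a two-sided 5% test. The article gives no within-person correlation r, SD, effect size or power for any fidelity trend, so there is no plan figure to reproduce and r is varied.

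**Step 1: stable differences between staff only.** Let s² be the total variance and Stt the sum of squared deviations of the wave times. The mean time is 84/10 = 8.4 months, so Stt = 1,216 − 10 × 8.4² = 510.4.

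- True slope variance: (1−r)s²/(m·Stt).
- Variance used by a regression without a person term: s²/(m·Stt).
- Ratio of standard errors, used to true: 1/√(1−r). Both m and Stt cancel.
- Real rejection rate with no trend: 2{1 − Φ(1.96/√(1−r))}.

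| r | SE too large by | Real size of the 5% test | Simulated size, 18 staff |
|---|---|---|---|
| 0.3 | 1.20 | 1.9% | about 2% |
| 0.5 | 1.41 | 0.6% | 0.7–0.8% |
| 0.7 | 1.83 | 0.03% | 0.1% or less |

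The power of the naive test, when a correct test has 80%, is Φ(1.96 + 0.84 − 1.96/√(1−r)). This gives 77% at r = 0.1, 68% at 0.3, 51% at 0.5 and 22% at 0.7, so the loss is 3, 12, 29 and 58 points. At r = 0.5 the loss is 22 points if the correct test has 90% power and 15 points if it has 95%.

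**Step 2: staff differ in their own trends.** A between-person slope SD of τ per month adds τ²/m to the true variance, which the naive test largely misses. With no average trend:

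- At τ = 0.02 total SD per month, the naive test still rejects only about 4%, 2–3% and 1% at r = 0.3, 0.5 and 0.7.
- At τ = 0.05 (1.15 SD over the 23 months between first and last wave), it rejects 10–14%.
- The two errors cancel at about τ = 0.026, 0.033 and 0.039 for the same three values of r.

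**Step 3: effects shared by all staff in a wave.** Let a share w of the total variance be common to everyone in a wave. It is not averaged over staff, so

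true/naive slope variance = 1 − r + (m−1)w.

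For m = 18 and r = 0.5:

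- w = 0.05: 0.5 + 17 × 0.05 = 1.35, SE too small by √1.35 = 1.16, rejection 2{1 − Φ(1.96/1.16)} ≈ 9% (simulated 10%).
- w = 0.10: 0.5 + 17 × 0.10 = 2.20, SE too small by 1.48, rejection ≈ 19% (simulated 20%).
- Break-even: w = r/(m−1) = 0.5/17 = 2.9%.

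In the same two settings, a test that allows for person-specific slopes but has no wave term rejects in 24% and 39% of simulations. A person term alone is therefore not a safe replacement.

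**The case against.** The strongest case against has four parts.

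1. *The faulty model is partly inferred.* The article never says that staff identity will be ignored; time is the main explanatory variable, not the only one, and an unseen analysis plan may set the random effects. This stands as a reason for restraint. It does not remove the point, because the article states a method together with a reason for it, and the reason fails for one of the data sources covered.

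2. *A reader might infer a definite loss of power, of about 30 points.* The documents do not support this. The figure needs r near 0.5, about 80% power for the correct test, no differing staff trends and no wave effects. Other values of r give 3 to 58 points, and Step 3 shows that the error can reverse. Since the survey measures the climate of one team in one clinic, shared wave effects are plausible.

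3. *A reader might infer that a non-significant staff measure is shut out of the outcome models and the clinic is reported as stable.* That goes too far. The second analysis also lets in components that contribute to the outcomes, and descriptive statistics come first. With full response, the slope estimate itself is unaffected.

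4. *Turnover* would reduce the repetition. It would not restore independence among those who stay.

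**Conclusion.** The point holds as a mismatch between a stated reason and the data it is applied to. The different-individuals argument is valid for the patient questionnaire and not for the staff survey. A time regression without a person term gives miscalibrated standard errors and p values for the staff trends.

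Under stable staff differences alone, the standard error is too large by 1/√(1−r) and the test is conservative. Shared wave effects above roughly r/(m−1) of the variance, or strongly differing individual trends, make it too liberal. Both size and direction rest on a correlation structure that the article does not give; every value of r, τ and w above is an assumption. Nor can it be said that all reported staff p values will be wrong, since the final model is not fully described.

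Severity is minor. The fidelity trend is a supporting analysis, and total cost and quality of life are not tested with it. The link to them is through covariate choice only, and that has a second route.

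**What to change.** In the Analysis section, limit the different-individuals reason, and the simple regression, to the patient questionnaire and the chart audits. For the personnel questionnaire, specify a mixed model, using the HLM approach already cited, with:

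- time as a fixed effect;
- a random intercept and a random slope for each staff member;
- a wave-level random effect, or else a sensitivity analysis that regresses the 10 wave means on time. The latter allows for shared wave effects but not for differing individual trends, so it supplements the person terms and does not replace them.

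If time is entered as dummy variables, each wave has its own coefficient and no separate wave effect can be estimated. The test then shows that waves differ, not that there is a trend.

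Keep a coded staff ID across waves. The article describes a coded list only for the claims data, and staff responses collected without a link may not be recoverable later.

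The cost is a change of wording, slightly more analysis work and linkage of staff responses over time. The wave term also costs some power, because a linear trend is then judged against variation among 10 waves, on about 10 − 2 = 8 degrees of freedom.
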